#### Secondary outcomes

The main secondary outcomes will be changes in knowledge levels and current practices relating to salt and changes in the mean concentration of sodium in foods.

Additional outcomes will include changes in the composition of diet based on the FFQs and understanding of the relationship between salt intake measured by spot and 24-hour urine in each country. The latter is important as, if it proves possible to use spot urines to estimate 24-hour urinary sodium excretion, in future this would provide a more feasible and practical alternative to measuring salt intake for countries.

#### Sampling strategy

The study population will be adults aged 18–69 years in both countries. Baseline salt assessment and questions on knowledge, attitudes and behaviours related to salt (KAB) will be integrated into the WHO STEPS survey in Samoa and the STEPS sampling framework will be used in Fiji. The framework uses a stratified (province or division) three-stage (enumeration area, household and individual) cluster random sampling process using probability proportional to size to obtain representative samples for the STEPS survey in each country based on the statistical regions identified in recent Censuses [36-38]. Sub-samples (e.g. every fifth person, so as to recruit 250 men and 250 women) will then be selected to collect 24-hour and spot urines.

#### Recruitment

Before beginning recruitment, permission will be sought from the local village chief to enter the village or enumeration area to carry out the work. Study enrolment and data collection will be conducted face-to-face in English (which is spoken by more than 90% of people in Fiji and Samoa) by trained health research staff. The research assistants will assist participants by orally translating written material into the local language, if needed. Participant information sheets and consent forms will be available in Hindi and Fijian (for Fiji) and Samoan. Each consented participant will be assigned a unique identification number so that survey results can be kept separate from personal details to ensure data confidentiality.

#### Data collection and management

Interviewer administered questionnaires will be used to obtain demographic and risk factor related information, including knowledge, awareness and practices related to salt from all participants. In addition, dietary intake will be assessed by trained research assistants using food frequency questionnaires (FFQs) on the sub-sample. The FFQ has been previously used to measure population salt intake in Fiji [39]. It will be adapted for Samoa, informed by the list of foods collected during the STEPS survey. Spot and 24-hour urine samples will be collected for each participant in both countries in accordance with established protocols [40]. All methods will be piloted as part of the training processes in each country.

#### Sample size

The sample size for each survey has been calculated to provide precise estimates of the average level of salt separately in adult Samoans and Fijians, based on the 24-hour urine collections. Five hundred participants recruited in both Fiji and Samoa will allow reporting of the mean level of sodium intake to within +/− 4.2 mmol with 95% confidence for each country. This estimate assumes a mean intake of 160 mmol sodium per day with a standard deviation of 48 mmol (1 gram of salt = 17.1 mmol sodium). This sample size will also enable the mean level of sodium to be reported to within +/− 5.85 mmol, for men and women and for rural and urban areas (where the sample is effectively divided in two with a sample size of 250 in each group), and to within +/− 8.42 mmol for subgroups such as older vs. younger men or rural versus urban women (where there will be a sample size of about 125 for each group). There will also be 80% power (alpha = 0.05) to detect approximately 8.5 mmol (0.5 gram salt) or greater differences between the average sodium levels between baseline and follow-up for each country.

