#### Analysis methods

The spot and the 24-hour urine samples from each individual will be analysed separately for sodium, potassium and creatinine. All analyses will be done by local laboratories in Samoa and Fiji using the ion selective electrode method for sodium and potassium analysis and the buffered kinetic Jaffe reaction without de-proteinisation for urine creatinine assay. Age and sex specific estimates obtained from the survey will be weighted based on population data from the most recent census. Descriptive statistics will be reported for anthropometrics, consumer awareness and urinary sodium levels. Results will be reported by sex age groups and evidence for differences between subgroups examined using t-tests.

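### The sample size treats 500 people recruited per country and survey as 500 analysable 24-hour collections, with no allowance for loss after recruitment

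*Protocol article*

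**What the plan says.** The Sample size section says the calculation is made for each survey, "separately in adult Samoans and Fijians, based on the 24-hour urine collections". It "assumes a mean intake of 160 mmol sodium per day with a standard deviation of 48 mmol". The number is given as people enrolled: "Five hundred participants recruited in both Fiji and Samoa will allow reporting of the mean level of sodium intake". The half-width attached to that number is ±"4.2 mmol with 95% confidence for each country". The section goes on to give ±"5.85 mmol, for men and women and for rural and urban areas", at 250 per group, and ±8.42 mmol for subgroups of about 125. It also claims 80% power at alpha 0.05 for a difference of about 8.5 mmol (0.5 g salt) between baseline and follow-up in each country.

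The Sampling strategy section for the population surveys sets the same number as a recruitment target: "Sub-samples (e.g. every fifth person, so as to recruit 250 men and 250 women) will then be selected to collect 24-hour and spot urines". The Data collection and management section expects both urine samples from every participant, following a cited collection protocol. The Analysis methods section adds: "The spot and the 24-hour urine samples from each individual will be analysed separately for sodium, potassium and creatinine".

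None of these sections gives an expected proportion of valid collections, a recruitment margin or a replacement rule.

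**The concern.** The number that determines precision and power is the number of 24-hour collections that enter the analysis. The article puts the number of people recruited in its place. Anyone who is enrolled but returns no collection, or one that cannot be used, lowers the first number and leaves the second unchanged.

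This matters because the primary outcome is the change in 24-hour urinary salt in each country, and the Discussion relies on the sample size being large enough to detect a small change. If some collections are lost, the stated half-widths are too narrow and the stated power too high. A true change of about half a gram is then more likely to be missed than the article says.

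**Working it through.** **Inputs.** From the Sample size section: n = 500 per country and survey, SD 48 mmol, mean 160 mmol, alpha 0.05, 80% power, difference about 8.5 mmol, and 1 g salt = 17.1 mmol sodium. The sidedness of alpha is not stated; two-sided reproduces the claim, whereas one-sided would give 87.6% power. The surveys are cross-sectional, so the two rounds are taken as independent samples. Loss rates are my assumption, equal in both rounds.

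**Formulas.**
- Half-width = 1.96 × SD / √n
- Detectable difference at 80% power = (1.960 + 0.8416) × SD × √(2/n) = 2.8016 × SD × √(2/n)
- Power at 8.5 mmol = Φ(8.5 / (SD × √(2/n)) − 1.96)

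**Reproducing the stated figures with n = 500.**
- Half-width: 1.96 × 48 / √500 = 4.21 mmol (stated 4.2).
- Detectable difference: 2.8016 × 48 × √(2/500) = 8.505 mmol (stated about 8.5).
- Power at 8.5 mmol: Φ(8.5/3.036 − 1.96) = Φ(0.840) = 79.95% (stated 80%). The n required per survey for exactly 8.5 mmol is 501.
- Subgroups: n = 125 gives 8.41 mmol (stated 8.42). n = 250 gives 5.95 mmol, not the stated 5.85. That small mismatch is a separate matter, but it should be corrected when the figures are restated.

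The country figures therefore use all 500 recruits per country as analysed collections, with nothing in reserve.

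**With assumed loss after recruitment, no design effect.**

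| Loss | Valid n per round | Half-width (mmol) | Detectable difference (mmol) | Power at 8.5 mmol |
|---|---|---|---|---|
| 0% | 500 | 4.21 | 8.51 | 80.0% |
| 1% | 495 | 4.23 | 8.55 | 79.6% |
| 5% | 475 | 4.32 | 8.73 | 77.9% |
| 10% | 450 | 4.43 | 8.97 | 75.7% |
| 20% | 400 | 4.70 | 9.51 | 70.7% |
| 30% | 350 | 5.03 | 10.17 | 64.9% |

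With 400 valid collections split evenly, the subgroup half-widths are 1.96 × 48 / √200 = 6.65 mmol for halves and 1.96 × 48 / √100 = 9.41 mmol for quarters.

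**The case against.** The strongest reply is that the effect is modest and partly hidden by rounding. ±4.2 still holds to one decimal down to about 490 collections (1.96 × 48 / √490 = 4.25). The target is given as approximate and equated with 0.5 g salt, which is 0.5 × 17.1 = 8.55 mmol; a 1% loss still gives 80% power for that. At 10% loss the detectable difference is 8.97 / 17.1 = 0.52 g, and at 20% it is 9.51 / 17.1 = 0.56 g. All of this stands. A reader might infer that any loss puts the stated figures out of reach, but the numbers show a gradual decline that becomes noticeable from about 5%.

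Three other stronger readings are also unsupported:
- **Refusals.** People who decline before enrolment are not among the 500 recruited, so they do not reduce n. Only failure to give a valid collection after recruitment does.
- **Bias in the change.** A reader might infer that incomplete collections will distort the comparison between rounds. That would need incomplete samples to be kept, or exclusions to be related to intake, and this to differ between baseline and follow-up. The article says none of these things. It cites established collection procedures and measures creatinine, and a condensed article may leave completeness rules to the cited procedure, the full protocol or the SAP.
- **Clustering.** A design effect would widen the figures further, but it is a different question and should not be added to the size of this one.

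The reply does not remove the core. The article itself states the sample size, its inputs and what they deliver, so equating recruited with analysed is in the text shown. It is not a detail left to another document.

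**Conclusion.** The point holds in a limited form. The ±4.2 mmol and the 80% power for about 8.5 mmol require 500 valid collections per country in each round, and the article attaches them to 500 people recruited. At an assumed loss of 5% to 10%, power at 8.5 mmol is 78% to 76%. At 20% to 30% it is 71% to 65%, with detectable differences of 9.5 to 10.2 mmol.

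These sizes rest on SD 48 mmol, two-sided alpha 0.05, independent rounds, equal loss in both rounds and no design effect. The actual loss rate is not in the article, so the true position within the range cannot be fixed. What is shown is a stated precision and power without margin. The documents do not show a failed design or a biased estimate of change.

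**What to change.** In the Sample size section, state the expected number of valid 24-hour collections per country and round, and restate the country half-width, the subgroup half-widths and the detectable difference on that number. With 400 valid, for example: ±4.7 mmol for the country mean, ±6.65 mmol for halves, ±9.41 mmol for quarters, and 9.5 mmol detectable with 80% power. This costs wording and slightly less favourable figures.

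To keep the present figures instead, recruitment would have to rise to 500/(1 − loss): 527 at 5%, 556 at 10%, 625 at 20% and 715 at 30%. That costs fieldwork and laboratory time. Baseline surveys had already begun in July 2012, so it may be open only for later recruitment.

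As advice only, and not to correct an error shown: confirm that the same completeness rule, using the creatinine already being measured, applies in both rounds.

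### The rural and urban precision figures assume 250 people in each area, which the sampling plan does not secure, and the ±5.85 mmol is slightly too small even at 250

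*Protocol article*

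**What the plan says.** All places are in the protocol article, Methods/Design.

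- **Sample size, assumptions.** "This estimate assumes a mean intake of 160 mmol sodium per day with a standard deviation of 48 mmol". With 500 participants per country, this "will allow reporting of the mean level of sodium intake to within +/− 4.2 mmol with 95% confidence for each country".
- **Sample size, first-level groups.** The mean is to be "reported to within +/− 5.85 mmol, for men and women and for rural and urban areas". The group size given for both splits is 250: "for rural and urban areas (where the sample is effectively divided in two with a sample size of 250 in each group").
- **Sample size, second-level groups.** A half-width of ±8.42 mmol is given for groups such as "older vs. younger men or rural versus urban women (where there will be a sample size of about 125 for each group").
- **Sampling strategy.** The frame is stratified by province or division and uses a three-stage "cluster random sampling process using probability proportional to size to obtain representative samples". The urine sub-sample is then drawn "so as to recruit 250 men and 250 women". No rural/urban stratum, target or oversampling is stated.
- **Analysis methods (population survey).** "Age and sex specific estimates obtained from the survey will be weighted based on population data from the most recent census". Rural/urban is not named as a weighting variable.

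**The concern.** The Sample size section treats area like sex: two groups of 250 with the same precision. The sampling plan supports this for sex, because it sets a target of 250 men and 250 women. It has no matching device for area. Under probability-proportional-to-size selection aimed at a representative sample, the rural and urban counts follow the population split. The same 250/250 is assumed for two different countries, so about half of adults would have to be urban in each.

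What is at stake is a stated property of the survey. If the split is uneven, the smaller area's mean will be less precise than the article promises, and more clearly so for women in that area. The national precision and the before-after power do not rest on the area split.

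**Working it through.** **Inputs.** SD 48 mmol, n = 500 per country, 95% confidence, and groups of 250 and about 125, all from the Sample size section. The share p of adults in the smaller area is not in the document. It is assumed to be 20%, 30% or 40%, with 50% as the case in which the article's numbers hold.

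**Step 1: reproduce the article's figures.** Half-width = 1.96 × SD / √n, with simple random sampling.

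- n = 500: 1.96 × 48 / √500 = 4.21 (stated 4.2; agrees).
- n = 125: 1.96 × 48 / √125 = 8.41 (stated 8.42; agrees to rounding).
- n = 250: 1.96 × 48 / √250 = 5.95 (stated 5.85; does not agree). The t quantile gives 5.98.
- A half-width of 5.85 would need n = (1.96 × 48 / 5.85)² ≈ 259, or SD = 5.85 × √250 / 1.96 ≈ 47.2.
- Before-after comparison: 500 per survey, a difference of 8.5 mmol and two-sided alpha 0.05 give 79.95% power (stated 80%; agrees).

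So the formula behind the section is clear, and ±5.85 is the one figure that does not follow from it.

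**Step 2: let the area split follow the population.** The smaller area has 500p people and the larger 500(1 − p). With equal numbers of men and women, women in the smaller area number 250p.

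| p | Smaller area: n, half-width | Larger area: n, half-width | Women, smaller area: n, half-width |
|---|---|---|---|
| 20% | 100, ±9.41 | 400, ±4.70 | 50, ±13.3 |
| 30% | 150, ±7.68 | 350, ±5.03 | 75, ±10.9 |
| 40% | 200, ±6.65 | 300, ±5.43 | 100, ±9.4 |
| 50% | 250, ±5.95 | 250, ±5.95 | 125, ±8.41 |

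For the smaller area, 6.65 / 5.85 = 1.14 and 9.41 / 5.85 = 1.61, so it is 14% to 61% wider than stated. Against the correct ±5.95 the ratios are 1.12 and 1.58, so 12% to 58% wider. None of these figures includes a cluster design effect.

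**Step 3: effect on a rural-urban contrast.** The ratio of standard errors is √(1/n₁ + 1/n₂) / √(2/250): 1.25, 1.09 and 1.02 at p = 20%, 30% and 40%.

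**Step 4: the alternative, an equal allocation by choice.** If 250/250 by area were imposed and then weighted back to the population, the design effect on the national mean is 500 × [p²/250 + (1 − p)²/250] = 1.36, 1.16 and 1.04 at p = 20%, 30% and 40%. The national half-width 4.21 × √(design effect) becomes ±4.91, ±4.53 and ±4.29.

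**The case against.** The strongest reply is that the article may be right. Proportional sampling gives about 250/250 if about half of adults are urban, and the make-up of the census regions lies in sources not shown. This stands: the text supports only that the design does not guarantee the equal split, and every size above other than the ±5.95 rests on an assumed share.

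It can also be said that the consequence is modest. Rural/urban is not among the listed outcomes, the population survey's Analysis methods section names reporting by sex and age group, the group sizes are worded as approximate, the larger area gains precision, and the contrast between areas loses little unless the split is very uneven. This also stands, and it limits the point to correcting stated figures.

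A reader might go further and infer that the national mean is biased: if 250/250 were imposed, weighting by age and sex would leave the smaller area over-represented. The error would be (0.5 − p) × D, where D is the rural-urban difference in mean sodium. With p = 20% to 40% and an assumed D of 8.5 to 17 mmol, that is 0.85 to 5.1 mmol. The document does not support this as a finding. It nowhere says that an equal area split will be imposed, and it describes the sample as representative. The error is zero if p is 50% or the areas do not differ. It also cancels from the primary outcome, the change between surveys, if the split and D are the same in both rounds.

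Nor does the text justify a complaint about household-level selection weights, which a condensed article commonly leaves to a fuller document, or about the census standard shifting between rounds, since nothing shows that a new census falls between them.

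**Conclusion.** The point holds as a mismatch between the Sample size and Sampling strategy sections. The 250 rural and 250 urban participants, and the roughly 125 rural and 125 urban women, have no basis in the stated design unless about half of adults are urban in both countries. If the smaller area holds 20% to 40% of adults (an assumption), its half-width is ±9.4 to ±6.7 mmol rather than ±5.85, and for women there ±13.3 to ±9.4 rather than ±8.42, before clustering.

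Separately, and without any assumption about area, ±5.85 should be ±5.95 for groups of 250 at the article's own SD. This applies to men and women as well.

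It would be too strong to say that the sampling cannot yield 250/250, or that the sections are irreconcilable: near an even split they agree. The primary before-after comparison is not called into question by this point.

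**What to change.** In the Sample size section, give the expected rural and urban numbers for Fiji and for Samoa from the census split, with the half-width that follows from each. Do the same for rural and urban women. Correct ±5.85 to ±5.95 mmol wherever it refers to groups of 250.

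Only if an equal rural/urban allocation is actually intended: state it in Sampling strategy, add urban/rural to the age-sex census weighting in the population survey's Analysis methods, and restate the national half-width (about ±4.3 to ±4.9 mmol for a smaller-area share of 40% down to 20%).

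The work is a change of wording plus a look-up in census tables. The cost is that the smaller area's stated precision becomes less favourable. Under an equal allocation the national precision also widens somewhat.

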## Discussion

The potential for salt reduction to reduce the burden of NCDs has now been endorsed internationally [44], with projections in recent studies that interventions would save millions of lives a year and be cost-saving to governments in the long run [35,45]. Samoa and Fiji both have relatively strong approaches to NCD prevention and have already highlighted salt reduction as a priority. Existing data on salt intake from Pacific Island countries are, however, sparse and this study will directly benefit Fiji and Samoa and be a major step forward in enabling the development and implementation of local salt reduction programs [46]. Both countries have identified the need for accurate information on current salt intake and sources of sodium in the diet to inform their plans for interventions. As such, there is a high likelihood that this project will translate into practical interventions with the potential to save lives and avert disease burden in the short term.

Key strengths include important new scientific data and capacity building in relation to monitoring and surveillance, intervention implementation and cost-effectiveness evaluation of salt reduction interventions in Fiji and Samoa. The project will use the gold standard method of 24-hour urine collection to monitor salt intake. Integrating the monitoring into the WHO STEPS program will ensure the collection of high quality data on a representative population sample and be crucial in ensuring the future sustainability of the salt monitoring as it is recommended that STEPs NCD risk factor surveys are repeated every five years. The participatory nature of the approach involving a diverse range of stakeholders will result in important contextual information which should improve the effectiveness of the intervention strategies. In both countries, the project will involve government throughout the process of developing and implementing policiesx and interventions, which should facilitate knowledge translation and ensure that salt reduction remains on the government agenda. The sample size will ensure adequate power to detect a small but clinically significant change in salt intake over a relatively short period.

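### The sample-size section's precision and power assume simple random sampling, although the survey is a weighted, stratified cluster sample; the figures need an explicit design effect

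*Protocol article*

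**What the plan says.** The Sample size section of the protocol article begins with precision: "Five hundred participants recruited in both Fiji and Samoa will allow reporting of the mean level of sodium intake". The 95% half-width it gives for a single country is ±4.2 mmol. On the inputs it says: "This estimate assumes a mean intake of 160 mmol sodium per day with a standard deviation of 48 mmol". Two further half-widths follow: ± "5.85 mmol, for men and women and for rural and urban areas", at 250 per group, and ± "8.42 mmol for subgroups such as older vs. younger men or rural versus urban women", at about 125 per group. The section closes with the comparison of the two survey rounds: "There will also be 80% power (alpha = 0.05) to detect approximately 8.5 mmol (0.5 gram salt) or greater differences".

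The population survey's Sampling strategy section describes how people are selected: "The framework uses a stratified (province or division) three-stage (enumeration area, household and individual) cluster random sampling process using probability proportional to size". The urine participants are a sub-sample of that sample (every fifth person is given as an example), aimed at 250 men and 250 women. The survey's Analysis methods section weights the age- and sex-specific estimates to the census.

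The Discussion then relies on the calculation: "The sample size will ensure adequate power to detect a small but clinically significant change in salt intake over a relatively short period".

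**The concern.** A half-width or power figure is valid for the design whose variance it uses. People in the same household or enumeration area plausibly share food supply and eating habits, so their sodium excretion is likely to be positively correlated. Unequal weights usually add variance too. The Sample size section mentions no design effect, intra-cluster correlation, cluster size or loss from weighting, and its figures leave no room for any of them.

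The change in 24-hour urinary salt in each country is the primary outcome, and the cost-effectiveness assessment goes ahead only if a positive impact is shown. An overstated power figure therefore bears on the main comparison and on whether the economic analysis takes place. This is not a detail left to a fuller document: the article prints specific figures, and those figures belong to a different sampling design from the one it describes.

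**Working it through.** **Inputs.** From the Sample size section: n = 500 per country per survey, SD = 48 mmol, 80% power, alpha = 0.05, and 17.1 mmol sodium per gram of salt. The rounds are separate cross-sectional surveys (Abstract, Methods/Design), so the comparison is 500 against 500. Sidedness is not stated. Two-sided alpha reproduces the stated power; one-sided alpha gives 87.6% and does not.

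**Step 1: reproduce the stated figures with no design effect.**

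- Half-width, n = 500: 1.96 × 48 / √500 = 4.21 mmol (stated 4.2).
- Half-width, n = 125: 1.96 × 48 / √125 = 8.41 mmol (8.415 before rounding; stated 8.42).
- Half-width, n = 250: 1.96 × 48 / √250 = 5.95 mmol (stated 5.85, which does not match).
- Standard error of the difference: 48 × √(2/500) = 3.036 mmol.
- Detectable difference at 80% power: (1.960 + 0.842) × 3.036 = 8.51 mmol (stated 8.5).
- Power at 8.5 mmol: Φ(8.5/3.036 − 1.96) = Φ(0.84) = 79.95% (stated 80%).
- Sample size for 8.5 mmol at 80% power: 501 per survey (planned 500).

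Apart from the n = 250 half-width, everything matches at a design effect of 1.00, with no reserve. The 5.85 figure would need n ≈ (1.96 × 48 / 5.85)² = 259 or an SD of 5.85 × √250 / 1.96 = 47.2 mmol.

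**Step 2: insert a design effect D.** The half-width becomes 1.96 × 48 × √(D/n), the detectable difference 8.505 × √D, and power at 8.5 mmol Φ(8.5/(3.036 × √D) − 1.96). The documents give no value for D, so those below are assumptions.

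| D (assumed) | Half-width, n = 500 | Power at 8.5 mmol | Detectable difference (80% power) |
|---|---|---|---|
| 1.00 | ±4.21 | 80% | 8.5 mmol (0.50 g) |
| 1.04 | ±4.29 | 78% | 8.7 mmol (0.51 g) |
| 1.2 | ±4.61 | 72% | 9.3 mmol (0.54 g) |
| 1.5 | ±5.15 | 63% | 10.4 mmol (0.61 g) |
| 2.0 | ±5.95 | 51% | 12.0 mmol (0.70 g) |

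Power falls below 78% once D exceeds about 1.05.

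**Step 3: where D might lie.** From clustering alone, D = 1 + (m − 1) × ICC, where m is the number of urine participants per enumeration area. Neither m nor the ICC is given. For m from 5 to 20 and ICC from 0.01 to 0.10 (both assumed), D runs from 1 + 4 × 0.01 = 1.04 to 1 + 19 × 0.10 = 2.9, and power at 8.5 mmol from 78% down to 38%. This grid takes no account of weighting losses or stratification gains.

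**The case against.** The strongest reply is that the size of the shortfall cannot be established from the article. The design also has features that work in its favour: stratification by province or division can lower variance, selection with probability proportional to size can limit variation in the weights, and a thinned sub-sample puts fewer people in each area. Weighting to census age and sex can itself reduce variance if sodium differs by age and sex. At the mild end of the assumed range the loss is under two percentage points of power. The SD is a planning value too: at 48/√1.2 = 43.8 mmol, a design effect of 1.2 would still give 8.5 mmol, while a larger SD would make matters worse.

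All of that stands, and it limits the point. A reader might infer that the design fails to deliver the stated figures, or that the study is underpowered. The documents do not support either statement, because the net design effect is unknown and could be close to 1. A reader might also infer that the Discussion's power sentence is false. That is not shown either: it names no threshold, and even 12.0 mmol is 12.0/160 = 7.5% of the assumed mean, against 8.5/160 = 5.3% as planned.

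The reply does not rescue the calculation as printed. The article does not argue that the favourable features cancel clustering and weighting; it simply uses the simple-random-sample variance. A design effect above 1 is the ordinary expectation for such a sample.

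**Conclusion.** The point holds in conditional form. The ±4.2 and ±8.42 mmol half-widths and the 80% power for 8.5 mmol are simple-random-sample figures attached to a weighted, stratified cluster sample. True precision and power are lower than stated unless stratification and the thin sub-sample fully offset clustering and weighting.

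Across assumed design effects from 1.04 to 2.0, power for 8.5 mmol runs from 78% to 51%. These values rest on the article's SD of 48 mmol, two-sided alpha, 500 participants in each round and the same design effect in both rounds.

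Separately, and whatever the design effect, the n = 250 half-width does not follow from the article's own SD. That slip is small and does not affect the primary comparison.

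**What to change.** 1. In the Sample size section, state an explicit design effect covering clustering and weighting, net of stratification, and give its basis.
2. Restate all half-widths and the 80% detectable difference with it. At an assumed 1.5, for example, they become ±5.2 mmol (n = 500), ±7.3 mmol (n = 250), ±10.3 mmol (n = 125) and 10.4 mmol (0.61 g).
3. Correct the n = 250 half-width, which is ±5.95 mmol even at design effect 1.
4. Before follow-up, replace the assumed SD and design effect with the baseline estimates and restate the detectable difference.
5. Tie the Discussion's adequate-power sentence to the restated detectable difference.

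The cost is a rewritten section with less favourable figures; no extra participants are needed. Keeping 80% power at 8.5 mmol would be a different decision, needing about 602, 752 or 1,002 people per survey per country at design effects of 1.2, 1.5 or 2.0. Returning to the same enumeration areas at follow-up might recover some precision for the change. It is an optional design choice that the article does not describe, and it is not part of this fix.
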